2.2. Diagnoses

2.2.1. Conventional imaging methods

The imaging diagnosis rate of peritoneal dissemination of stomach cancer is low and the odds ratio of CT for diagnosing peritoneal dissemination was 66.18 (95%CI: 27.28-160.53), being the highest in a meta-analysis of 33 reports (US: 8, EUS: 5, CT: 22, MRI: 2, FDG-PET: 5) 2). In all diagnostic methods, the diagnostic specificity was 0.96-0.99, being high, but even the diagnostic sensitivity of EUS with the highest sensitivity was only 0.34 (0.10-0.69) and that of CT was 0.33 (0.16-0.56), showing that peritoneal recurrence may be overlooked on axial CT normally employed for postoperative follow-up of stomach cancer in 2 out of 3 cases. In a randomized controlled study performed in Korea 3), CT and FDG-PET were compared. Intra-abdominal nodules, ascites, irregularity with beaded thickening of the mesentery and omentum or fluffy images were regarded as peritoneal dissemination on CT. On PET, diffuse metabolic enhancement along the intestine and mesentery was set as a judgment criterion. The sensitivity of CT was 76.5%, being significantly higher than that (35.3%) of PET (p=0.037), but the specificity was 91.6%, being inferior to that (98.9%) of PET (p=0.035). Yoshikawa et al. 4) analyzed 123 initial-onset stomach cancer cases with peritoneal metastasis and observed that the accuracy of diagnosing peritoneal dissemination as positive on preoperative diagnosis by CT was 37.4%, being low, but the outcome was significantly poorer in the positive than negative group, showing its significance as a prognostic factor.

2.2.2. Tumor markers

Regarding serum tumor marker, elevation of the CA125 level in stomach cancer patients is correlated with the presence and expansion of peritoneal dissemination. Takahashi 5) reported that the CA125-positive rate in patients with peritoneal dissemination of stomach cancer was high (42.9%) whereas those of other markers (CEA, CA19-9, and AFP) are 10% or lower, showing high metastatic organ specificity. The reason is considered as follows: CA125 is not produced by tumor cells, but it is present in peritoneal mesothelial cells, so that it represents peritoneal inflammation. Accordingly, infectious peritonitis, endometriosis of females, and early period after surgery (the half-life of CA125 is 5-10 days 6)) have to be excluded. Ueki et al. 7) measured CA125 in 219 patients with surgical stomach cancer before surgery and observed that the sensitivity and specificity of CA125 were 31.9 and 93.6%, respectively, in 47 peritoneal dissemination-positive patients. Nakata et al. 8) reported that the sensitivity and specificity of CA125 for peritoneal dissemination of stomach cancer were 39.4 and 95.7%, respectively, showing its superiority to imaging diagnosis including CT and US. Emoto et al. 9) reported that combination with multiple markers, such as CA72-4, increases the sensitivity, but the sensitivity of CA125 alone was only 46%.

On the other hand, it has been frequently reported that the sensitivity of CA125 is correlated with the degree of advancement of peritoneal dissemination, so that it does not become positive when the absolute amount of tumor is still small. According to Nakata et al., the accuracy of CA125-based diagnosis was 28.6% when the stage was P1 (vicinity of the stomach, small amount), and those of CT and US were 0%. In a study reported by Emoto et al., correlation was high when ascites was present, but the CA125 level exceeded the cutoff value in only 1 (12.5%) of 8 P1 cases, suggesting that CA125 cannot be expected to supplement imaging diagnosis of peritoneal dissemination of stomach cancer.

2.2.3. Contrast enema

Since intestinal stenosis occurs as peritoneal dissemination advances in many cases, when stenosis is observed in stomach cancer patients on contrast enema, peritoneal dissemination is strongly suspected. However, the diagnostic sensitivity of contrast enema is unclear when it is performed while the absolute amount of disseminated tumor is still small, even though characteristic findings, such as “striped colon 10)” and “fixed transverse parallel folds 11)”, are observed. Miyagawa 12) reported comparisons between contrast enema and CT findings in 60 patients diagnosed with large intestinal metastasis of stomach cancer. The definite diagnosis of metastasis was made by surgery in 28, autopsy in 5, and clinical judgment, such as imaging, in 27. When 5 mm or more wall thickness on CT was set as a diagnostic criterion, the diagnosis could be made in more than 80%, but the diagnostic sensitivity of enema was 98% (59/60), being superior to that (83% (50/60)) of CT. On the other hand, CT was considered advantageous when the purpose was diagnosis of peritoneal dissemination, because intra-abdominal masses were noted in 62% of the patients and ascites was noted in 37%, showing that the lesions are derived from peritoneal dissemination in many patients. One reason for the absence of overlooking on enema is that the difference between normal and metastatic regions is emphasized by dilating the large intestine by injecting air. If CT images are acquired while air is injected into the large intestine, improvement of the sensitivity of CT for peritoneal dissemination can be expected.

2.2.4. CT colonography

CT colonography (CTC) is an imaging diagnosis method initially reported in 1994. It acquires 3D and virtual endoscopic images of the large intestine by computer data processing of CT images. It is low-invasive and capable of detecting colorectal lesions at an accuracy comparable to that of colonoscopy. In the 2011 NCCN guidelines 13), every 5-year CTC is stated with every 10-year colonoscopy as a screening method to discover neoplastic polyps and cancer. In addition, information other than that of the large intestine can be acquired and this is also a big advantage. Pickhardt et al. 14) reported that cancers other than colorectal cancer were identified at a rate of one in 300 cases. However, to our knowledge, no study performing CTC to detect minute extramural changes in the large intestine has been reported as of January 2020.

Advantages of diagnostic images of CTC include high objectivity and reproducibility, being a technique appropriate for standardization. In Japan, imaging of the lower digestive tract by CTC has been covered by national health insurance since January 2012, and 600 medical fee points are added when carbon dioxide is injected using a tube for the rectum and 3-dimensional imaging process is performed using 16- or more row multi-slice CT.

2.3. Study design

2.3.1. Endpoint

The primary endpoint of this study was the diagnostic sensitivity of CTC for PM. The secondary endpoints included overall survival (OS) and progression-free survival (PFS). The diagnostic sensitivity of CTC has been estimated to be 60%, with a threshold value of 50% and an expected value of 75%. Using Simon’s two-stage method with a one-sided alpha value of 0.05 and a beta value of 0.7, we determined that a sample of 18 patients was required for this study.

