0.3. Subjects

1. Histologically diagnosed with stomach cancer by endoscopic biopsy or surgical biopsy.
2. Peritoneal metastasis/recurrence of stomach cancer is suspected based on physical, laboratory test, and imaging findings.
3. The ECOG performance status is 0, 1, or 2.
4. Oral ingestion is possible.
5. Written consent is obtained from the patient.

0.4.Target number of enrollment

The diagnostic sensitivity of CTC has been estimated to be 60%, with a threshold value of 50% and an expected value of 75%. Using Simon’s two-stage method with a one-sided alpha value of 0.05 and a beta value of 0.7, we determined that a sample of 18 patients was required for this study.

1.Aim

In this study, we aimed to use CTC for early detection of PM in patients in whom PM was suspected based on clinical symptoms and general CT findings but not yet diagnosed, and to administer anticancer agents in a timely and effective manner.

2.Background and bases of plan

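### The sample size is justified with a beta of 0.7 (30% power), which gives 7 patients; the stated 18 is the Simon minimax size for a beta of 0.3

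*Protocol*

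**What the plan says.** The primary endpoint is the diagnostic sensitivity of CT colonography for PM (protocol 2.3.1, Endpoint). The same section gives the whole sample-size justification: a threshold sensitivity of 50%, an expected sensitivity of 75%, and Simon's two-stage method "with a one-sided alpha value of 0.05 and a beta value of 0.7", leading to 18 patients. Section 0.4 (Target number of enrollment) gives the same inputs, including "a one-sided alpha value of 0.05 and a beta value of 0.7", and the same 18.

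Both sections also mention an estimated sensitivity of 60%, without saying what part it plays in the calculation. Neither gives a power figure, the stage sizes, the decision boundaries, or whether the design is Simon's optimal or minimax variant. The beta value is therefore the only statement of the type II error in the protocol.

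**The concern.** Beta is the probability of failing to reject the null hypothesis when the alternative is true. Read literally, the design would miss a test with 75% sensitivity seven times in ten. No one would normally plan a study that way, and 0.7 looks like a power. If so, the stated inputs should not lead to 18 patients.

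The stake is the only justification of the study's size. An ethics committee reading it is told that the study has 30% power and that 18 patients are needed to reach it; both statements cannot be right. Because the protocol prints no boundaries, anyone who rebuilds the decision rule from the stated inputs gets a different design, with a two-patient first stage and a maximum of seven.

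**Working it through.** **Inputs (protocol 2.3.1, repeated in 0.4).** Null sensitivity p0 = 0.50; alternative p1 = 0.75; one-sided alpha = 0.05; beta = 0.7; stated n = 18.

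**Method.** In a Simon design, n1 patients enter stage 1 and the study stops if at most r1 are positive. Otherwise n2 = n − n1 more are added, and the null is rejected if the total exceeds r. The probability of rejection at sensitivity p is

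R(p) = Σ (x from r1+1 to n1) P(X1 = x) · P(X2 ≥ r + 1 − x), with X1 ~ Bin(n1, p) and X2 ~ Bin(n2, p).

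All designs with R(p0) ≤ alpha and R(p1) ≥ 1 − beta were searched. The minimax design has the smallest n; the optimal design has the smallest expected size under p0.

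**1. As written, beta = 0.7 (power at least 0.30).** Minimax and optimal coincide: n1 = 2, r1 = 1, n = 7, r = 5. By hand, both of the first 2 must be positive, then at least 4 of the next 5:
- alpha: 0.5² × 6/32 = 0.25 × 0.1875 = 0.0469
- power: 0.75² × (5 × 0.75⁴ × 0.25 + 0.75⁵) = 0.5625 × 0.6328 = 0.356

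The stated 18 is not reproduced.

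**2. With beta = 0.3 (power at least 0.70).** Minimax: n1 = 7, r1 = 3, n = 18, r = 12, so n2 = 11.
- alpha: (35×67 + 21×232 + 7×562 + 1×1024) / (128 × 2048) = 12175/262144 = 0.0464
- power: 0.1730×0.4552 + 0.3115×0.7133 + 0.3115×0.8854 + 0.1335×0.9657 = 0.0788 + 0.2222 + 0.2758 + 0.1289 ≈ 0.706 (exact 0.7056)
- expected size under p0: 7 + 0.5 × 11 = 12.5

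This is exactly the stated 18.

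**3. Other readings.**

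| p0 / p1 | alpha | beta | Minimax n | Optimal n |
|---|---|---|---|---|
| 0.50 / 0.75 | 0.05 | 0.7 | 7 | 7 |
| 0.50 / 0.75 | 0.05 | 0.3 | **18** | 20 |
| 0.50 / 0.75 | 0.05 | 0.2 | 23 | 25 |
| 0.50 / 0.75 | 0.025 | 0.7 | 9 | 11 |
| 0.50 / 0.75 | 0.10 | 0.2 | 18 | 22 |
| 0.60 / 0.75 | 0.05 | 0.7 | 16 | 21 |
| 0.50 / 0.60 | 0.05 | 0.7 | 34 | 42 |

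**4. Without two stages.** An exact single-stage test needs 8 patients at 30% power, and 18 at 70% power (success with at least 13; alpha 0.0481, power 0.717). The normal approximation n = [(1.645×0.5 + z(power)×√(0.75×0.25)) / 0.25]² gives 5.7 for 30% power and 17.6, rounded up to 18, for 70% power.

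No calculation with a beta of 0.7 gives 18, even when the unexplained 60% is used as the null or the alternative.

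**The case against.** The strongest reply is that this is a slip of labelling. If 18 came from a power of 0.7, the sample size rests on the right quantity, the design loses no power, and only one word is wrong. That stands as far as the number 18 is concerned, and it makes the seriousness of the point open to argument. It does not make the text correct: the printed inputs do not give the printed result, and no other part of the protocol corrects them.

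A second reply is that 18 does not prove a minimax design at beta 0.3. A single-stage test at 70% power also needs 18, as does a minimax design with alpha 0.10 and beta 0.2, while the optimal variant at beta 0.3 needs 20. This stands as a caution about what the authors did, but none of it rescues the text. The single-stage route contradicts the stated two-stage method and still needs 70% power; alpha 0.10 contradicts the stated alpha. The variant, stage sizes and boundaries may be in the SAP, which is not shown, so their absence is not held against the protocol.

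A third reply is that speaking of 18 patients with PM adds something, because the protocol says only 18 patients and enrols people in whom PM is suspected but unconfirmed. The qualifier is accurate, since sensitivity is calculated only in patients who have PM and the power of 0.706 applies to 18 such patients. Whether the 18 counts enrolled or PM-positive patients is a separate question that this correction does not settle.

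**Conclusion.** The concern holds. The beta of 0.7 is wrong as written in sections 0.4 and 2.3.1. It means 30% power and leads to a maximum of 7 patients (attained power 0.356), against the stated 18. With the other stated inputs kept and 0.7 read as power, the minimax design gives 18 exactly, with attained alpha 0.0464 and power 0.7056, a type II error of 1 − 0.7056 = 0.294. The misstatement is therefore 30% against about 71% power.

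The mismatch follows from the protocol's own figures alone. Two further steps are inferences: that power was labelled beta, which is the smallest change that restores agreement, and that the variant was minimax, the one of the two standard Simon variants that gives 18 at beta 0.3. The power of 0.706 assumes that all 18 patients in the calculation have PM.

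**What to change.** In sections 0.4 and 2.3.1, replace the beta of 0.7 with a beta of 0.3 (power 70%). After the sponsor has confirmed the variant from the original calculation, name it. If it is minimax, state its attained alpha of 0.046 and power of 0.706 at 18 patients with PM, ideally with its boundaries (3/7 and 12/18). If another design was used, give that design's attained figures instead.

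The cost is a wording correction in two places. It does not change the figure of 18, the endpoint or the conduct of the study.

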2.3.2. Patient enrollment expectancy

The recurrence rate of post surgical gastric cancer patients is 10-20%. That will calculate approximately 30 patients a year. Among those cases, five to eight will be predicted to show PM.

3. Patient selection

The patients were cases wherein PM/gastric cancer recurrence was suspected based on physical examination, laboratory tests, and imaging findings, but a definite diagnosis could not be established.

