3.1. Inclusion criteria

(i) histologically diagnosed gastric cancer via endoscopic biopsy or surgical specimen retrieval; (ii) suspected PM/recurrence of gastric cancer based on at least one of the following clinical findings: abnormal physical symptoms with causes that could not be explained by other diseases, elevation of serum tumor markers, and suspicious but not definitive signs of PM on conventional CT images; (iii) Eastern Cooperative Oncology Group (ECOG) performance status of 0, 1, or 2; (iv) oral intake ability; and (v) provision of written consent by each patient.

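### The 18 is an enrolment target for patients with suspected PM, but the sensitivity calculation needs 18 patients who have PM, so the implied 70% power holds only if every enrolled patient has it

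*Protocol*

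**What the plan says.** Protocol section 2.3.1 defines the outcome: "The primary endpoint of this study was the diagnostic sensitivity of CTC for PM". It sets a threshold sensitivity of 50% and an expected sensitivity of 75%, names Simon's two-stage method with a "one-sided alpha value of 0.05 and a beta value of 0.7", and concludes that "we determined that a sample of 18 patients was required for this study". Section 0.4 gives the same calculation under the heading "Target number of enrollment".

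Section 3 describes the patients as people in whom PM or recurrence was suspected, "but a definite diagnosis could not be established". Section 3.1 admits a patient with "suspected PM/recurrence of gastric cancer based on at least one of the following clinical findings", so one finding is enough: unexplained symptoms, a raised tumour marker, or equivocal CT signs.

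The only PM frequency given for the study's own patient source is in section 2.3.2. After estimating about 30 post-surgical recurrences a year, it says: "Among those cases, five to eight will be predicted to show PM".

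**The concern.** Sensitivity is the proportion of patients with the disease whom the test calls positive. A patient without PM belongs to the specificity calculation and contributes nothing to a test of 50% against 75% sensitivity. The protocol enrols on suspicion, and the diagnostic question arises only because some of these patients may not have PM. A count of 18 enrolled is therefore not a count of 18 in the denominator.

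Two things are at stake. The primary test may have clearly less power than the design implies. There is also a temptation to restore the 18 by dividing by everyone enrolled, but the result would then be a CTC positivity rate, which is not the declared endpoint.

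**Working it through.** **Inputs.** Threshold p0 = 0.50, expected p1 = 0.75, one-sided alpha 0.05 and N = 18 come from section 2.3.1. That 18 counts enrolled patients comes from the heading of section 0.4. The prevalence of PM among enrolled patients, π, is not in the protocol; it is assumed here over 50% to 100%.

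**Step 1: reproduce the 18.** Take the Simon design that stops if there are 3 or fewer positives in the first 7 patients and otherwise declares success with 13 or more positives in 18. The probability of success at sensitivity p is

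Σ(x = 4 to 7) P(X1 = x | 7, p) × P(X2 ≥ 13 − x | 11, p).

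- At p = 0.50 this is 0.0464 (alpha).
- At p = 0.75 it is 0.7056 (power).

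This is the minimax design for power 0.70, so N = 18 is reproduced exactly. The stated beta of 0.7 gives 18 only if read as power 0.70; read literally (power 0.30), the minimax N would be 7. A single-stage exact test of 18 patients, needing at least 13 positives, has alpha 0.0481 and power 0.7175.

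In each version, all 18 are patients with PM. No margin is added for anyone else.

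**Step 2: power with 18 enrolled on suspicion.** Let M be the number with PM, M ~ Binomial(18, π). For each value m, find the smallest r with P(X ≥ r | m, 0.50) ≤ 0.05 and take the power as P(X ≥ r | m, 0.75). Average power is Σ P(M = m) × power(m). A single-stage test is used because the protocol gives no first-stage size or cut-offs.

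| Assumed PM prevalence among enrolled | Expected number with PM (18π) | Average power |
|---|---|---|
| 100% | 18.0 | 0.72 |
| 90% | 16.2 | 0.59 |
| 80% | 14.4 | 0.53 |
| 70% | 12.6 | 0.46 |
| 60% | 10.8 | 0.38 |
| 50% | 9.0 | 0.30 |

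**Step 3: power at fixed numbers of PM patients.**

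| Patients with PM | Positives needed | Power at 75% |
|---|---|---|
| 9 | 8 | 0.30 |
| 12 | 10 | 0.39 |
| 13 | 10 | 0.58 |
| 14 | 11 | 0.52 |
| 16 | 12 | 0.63 |
| 17 | 13 | 0.57 |
| 18 | 13 | 0.72 |
| 20 | 15 | 0.62 |

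The column does not rise steadily, because an exact test moves in whole patients. Eighteen is a local peak.

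**Step 4: enrolment if 18 PM patients are wanted.** Expected enrolment is 18/π, rounded up: 18/0.80 = 22.5, so 23; 18/0.70 = 25.7, so 26; 18/0.50 = 36.

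**The case against.** **The 18 may have been meant as PM cases.** Section 2.3.1 says only that 18 patients are needed, next to a sensitivity endpoint, and section 2.3.2 ends its accrual estimate in PM cases. That reading is possible, but section 0.4 labels the number as enrolment and no visible text says recruitment continues until 18 have PM. If PM cases were meant, the heading in 0.4 is wrong and enrolment is understated. The text needs correcting under either reading.

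**The arithmetic is sound.** This stands. The calculation is right for 18 patients with PM; the fault is the unit to which the result is attached.

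**Discreteness exaggerates the loss.** This stands in part. Going from 18 to 17 PM patients takes power from 0.72 to 0.57, while 20 PM patients would have only 0.62. Single counts should therefore not be over-read. Averaging over the number with PM smooths these jumps among the smaller counts, but 18 remains a peak as the comparator.

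**The denominator and critical values belong in an analysis plan.** Their absence alone would not be a finding. The enrolment figure and its justification, however, are fixed in the protocol, and no later document can recover power once 18 mixed patients have been enrolled.

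**Two stronger readings that the protocol does not support.** A reader might take 5 to 8 of about 30 as the trial's PM prevalence and infer almost no power. That ratio describes all post-surgical recurrences, not patients selected because PM is suspected. A reader might also calculate how often 13 of all 18 enrolled would be CTC-positive. That requires a false-positive rate, which the protocol does not give, and the result would not be sensitivity.

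**Conclusion.** The protocol attaches a correct calculation to the wrong unit. It needs 18 patients with PM, sets 18 as the number of suspected patients to enrol, and makes no allowance for the difference. Power of about 0.71 (Simon two-stage) or 0.72 (single-stage) is delivered only if every enrolled patient has PM.

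Average power is lower at every prevalence below 100% that was examined, from about 0.59 at 90% to 0.30 at 50%. The direction does not depend on the prevalence assumed within that range; the size does, and the protocol gives no figure to settle it. The values assume true sensitivity of 75%, a single-stage exact one-sided 5% test, and a usable CTC result in every patient with PM. It would go too far to say that the trial has any one particular power.

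**What to change.** Keep 18 as the enrolment target and amend sections 0.4 and 2.3.1 as follows.

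1. State that the denominator of the primary endpoint is enrolled patients with confirmed PM.
2. Replace the implied 70% power with the power for 18 enrolled over a stated range of assumed PM prevalence, as in the first table, and label the prevalence as an assumption.
3. State that the result will be judged against the exact one-sided critical value for the number of PM patients attained, for example at least 10 of 12, 11 of 14, 12 of 16 or 13 of 18 for a single-stage test. If the Simon interim stage is kept, give the equivalent two-stage rule.
4. While the sentence is open, write the 0.7 as power if that is what was meant.

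This costs wording and a less favourable stated power; no additional patients are needed. The alternative is to define 18 as patients with confirmed PM and enrol until that number is reached. That would keep the calculated power, but needs about 23 enrolled at 80% prevalence, 26 at 70% and 36 at 50%, so it is the expensive option.

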2.3.2. Patient enrollment expectancy

The recurrence rate of post surgical gastric cancer patients is 10-20%. That will calculate approximately 30 patients a year. Among those cases, five to eight will be predicted to show PM.

3. Patient selection

The patients were cases wherein PM/gastric cancer recurrence was suspected based on physical examination, laboratory tests, and imaging findings, but a definite diagnosis could not be established.

